### Saline injections

The study nurse will prepare a syringe with a saline solution (4 mL), attach a needle and place an opaque label around the syringe and needle base to mask the contents in a separate room. The nurse will then deliver the syringe to the treating physician for injection.

### Outcome measures

Study outcome measures are presented in Table 1. The primary endpoint measure are 12-month change in knee pain and function scores.i.Knee pain and function score: this will be measured at baseline, 1-, 3-, 6- and 12-month using the Western Ontario and McMaster Universities (WOMAC) Osteoarthritis Index with terminal descriptors ‘mild OA (score <32)’, ‘moderate OA (score 32~48)’ and ‘severe OA (score >48)’. This was chosen because it has well-established clinimetric properties in knee OA and established minimal clinically important differences, and is a recommended measure for knee OA RCTs from the Osteoarthritis Research Society International [16–18].

The following secondary outcome measures will also be collected:i.Health-related quality of life: this will be measured at baseline, 1-, 3-, 6- and 12-month using the short-form 36-item health survey questionnaire (SF-36) instrument [19, 20]. The SF-36 is divided into 8 fields, with higher scores indicating better quality of life.ii.Overall knee pain score during activities of daily living (using an 11-point VAS): this will be measured at baseline, 1-, 3-, 6- and 12-month. The VAS is to indicate the degree of pain in a total of 11 numbers from 0 to 10; 0 means no pain and 10 means worst pain with high reliability. The patient chooses a number to represent the degree of pain according to his pain.iii.Lysholm knee scoring scale: this will be measured at baseline, 1-, 3-, 6- and 12-month. The Lysholm knee scale demonstrated overall acceptable psychometric performance for outcomes assessment of various chondral disorders of the knee. This makes up for the shortcomings of the WOMAC score and established minimal clinically important differences with high reliability [17, 21].iv.MRI-derived measurements: an MRI scan of the target knee will be performed at baseline and 12-month using a 3 T whole-body system with a dedicated extremity coil and a T1-weighted fat-suppressed 3D gradient recall acquisition sequence.

MRI osteoarthritis knee score (MOAKS): an OA-specific semi-quantitative tool evaluating multi-feature joint changes associated with OA [22]. We will assess the following subscores:

Meniscal morphology: any region worsening at 12-month; scored as yes or no.

Intercondylar synovitis incorporating synovitis and effusion: worsening at 12-month; scored as yes or no.

Whole knee effusion: categorized as worsened, no change, or improved.

Progression of medial distal femur and proximal tibia bone marrow lesion size: scored as 0–3 per region, with higher scores indicating greater size.

Cartilage defects: score in the medial distal femur and the proximal tibia at baseline and 12-month using categorical scoring (range 0–4 per region, with higher scores indicating greater cartilage defects).

Progression of medial cartilage defects (yes/no) will be defined as an increase in score by at least 1 from baseline to follow-up in either the medial tibial or medial femoral compartment [23].

### Co-intervention

Participants will be asked to avoid the use of non-steroidal anti-inflammatory drugs and other analgesics for knee pain from 3 weeks before the baseline assessment until the 12-month follow-up assessment. Throughout the trial, key treatment (exercise therapy and healthy lifestyle advice) and co-interventions used by patients will be registered, such as non-steroidal anti-inflammatory drugs, other analgesic drugs, intra-articular injections or inlays.

### Safety

All adverse events are reported spontaneously by the patient or observed by the study nurse. This will include questions about any adverse events that participants believe may be related to the trial intervention, including their nature, how long they lasted for and what action if any, they took. To date, no serious adverse events have been reported in the literature concerning PRP intra-articular injections of the knee. The local Medical Ethical Commission will be notified of any serious adverse events. In the event this happens, the advice of the Medical Ethical Commission will be followed accordingly.

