The aim of this study is to evaluate the safety and efficacy of intra-articular injection of allogeneic PRP from blood donors in patients with knee osteoarthritis combined with hematologic blood dyscrasias with platelet dysfunction. (e.g. immune thrombocytopenia, aplastic anemia, etc.) Our hypothesis is that there is a clinically relevant difference in the primary and secondary outcomes between the two treatment groups. The minimal clinically important differences of patient reported outcomes will be considered in this study.

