### Procedures

Figure 1 and Table 1 outline the trial phases and the schedule for enrollment, screening, interventions and assessments. Participants will complete an onsite survey in the outpatient department to determine initial qualifications, and then a coordinating researcher will screen through a questionnaire. Participants deemed appropriate from the questionnaire screening will be allowed to undergo conventional radiographs (weight-bearing long-leg, A/P and lateral views) and blood screening. The screening will be performed in the outpatient department, where two experienced physicians evaluated patients’ eligibility for enrollment in this study through history taking, imaging examination, and laboratory tests. These steps could diminish possible bias about the inclusion criteria of age range. Participants who meet the inclusion and exclusion criteria will then be deemed suitable for the study. Eligible participants will complete the baseline clinical outcome scores, paper-based questionnaires and baseline knee MRI scans. Participants will also be asked to discontinue non-steroidal anti-inflammatory drugs and other analgesics for knee pain from 3 weeks before the baseline assessment until the 12-month follow-up assessment.

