### Randomization procedures

Randomization is centralized, and participants will be randomly allocated in a 1:1 ratio. An independent statistician will provide a computer-generated randomization list, using a permuted block design with block sizes of 4 and 6. The sequence is concealed by the use of a computer interface implemented in the electronic case report form. The patients, treating physicians and coordinating researchers will all be blinded to the allocation of the intervention. A study nurse will have access to the randomization result and the allocated intervention.

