### Interventions

Participants in both the allogeneic PRP and saline groups will receive one intra-articular knee injection at the same time after signing written informed consent (supplement 3), in line with commonly used injection protocols for this condition [6, 15]. The study nurse will give the treating physician an occluded syringe with a needle containing 4 ml of either normal saline or allogeneic PRP, and the contents will be injected into the knee joint. After the injection, passive knee flexion and extension will be performed six times with the participant observed resting for 20 min thereafter.

After injection, participants will be asked which group they believe they are in, and separately the injecting treating physician will also be asked which group they believe the participant is in to assess the success of blinding. This will be registered accordingly. The study nurse will ask the participant if they experienced any adverse events following the injection.

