### Loss to follow-up

The coordinating researchers will attempt to reduce loss to follow-up as much as possible by contacting every patient and being present at every patient visit. Each patient will be assisted by a coordinating researcher to ensure that each paper-based questionnaire is filled in. If the patient is lost to follow-up, an analysis of demographic and prognostic characteristics will be performed on these cases and the remaining patients. The patient eligible for and compliant with each follow-up will be documented.

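### The only adverse event questions described for follow-up ask about events the participant thinks may be related, so bleeds attributed to the platelet disorder may go unrecorded in both arms

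*Protocol article*

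**What the plan says.** The Background section makes safety a joint aim with efficacy: "The aim of this study is to evaluate the safety and efficacy of intra-articular injection of allogeneic PRP from blood donors". The Participants section requires a blood dyscrasia with platelet dysfunction.

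Three places describe how adverse events are found:

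- **Safety section.** "All adverse events are reported spontaneously by the patient or observed by the study nurse". It then describes questioning: "This will include questions about any adverse events that participants believe may be related to the trial intervention". No other question is described there.
- **Interventions section.** After the injection and a 20-minute rest: "The study nurse will ask the participant if they experienced any adverse events following the injection". This question carries no relatedness condition.
- **Table 1.** Adverse events are marked at the injection and at 1, 3, 6 and 12 months. A complications item is marked at the injection only. The table gives no method.

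Two other records bear on the point. Table 1 schedules drug and supplement use at baseline and at each follow-up visit. The Co-intervention section registers co-treatments throughout the trial, with an open list of examples that are all knee treatments.

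**The concern.** The relatedness condition hands a causal judgement to the participant before the event is recorded. That suits this population poorly. A patient with a long-standing platelet disorder has a ready alternative explanation for a nosebleed, a bruise or a transfusion, and may not think it worth mentioning. The participant is also blinded, so cannot know whether there was any allogeneic product to relate the event to.

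In a saline-controlled trial, relatedness is better judged by comparing the arms, which requires events to be recorded whatever the patient thinks caused them. If they are not, a report of few bleeds, or of no excess over saline, is weaker support for the safety aim than it appears.

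**Working it through.** **1. Compare the methods by time point.**

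| Time point | Adverse events scheduled (Table 1) | Question without a relatedness condition described |
|---|---|---|
| Injection | Yes | Yes (Interventions) |
| 1, 3, 6, 12 months | Yes | None |

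So 4 of the 5 scheduled time points have no unconditional question described. This is an inference: the Safety section does not tie its questions to particular visits.

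**2. Ask what the other routes would catch.** Spontaneous report depends on the patient choosing to mention the event. Nurse observation cannot see a bleed that resolved between visits, and the gaps are 1, 2, 3 and 6 months. The drug-use and co-intervention records could pick up a transfusion, though neither names it. They would miss a bleed that needed no treatment.

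**3. Reproduce the plan's sample size, to fix the number of patients.** The inputs in the Sample size calculations section are a difference of 11.5, SD 16, 90% power and 15% dropout, with two-sided α = 0.05 (Statistical analysis section).

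- Normal formula: n = 2 × (1.960 + 1.282)² × (16/11.5)² = 40.7, so 41 per arm.
- t-based version: 41.7, so 42 per arm and 84 in total, as stated.
- 42/0.85 = 49.4, so 50 per arm, as stated.
- After 15% dropout: 50 × 0.85 = 42.5, taken as 42.

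The sample size is not in question here.

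**4. Illustrate the effect of under-capture.** The document gives no bleeding risk and no capture rate, so both are assumed. Let c be the proportion of bleeds arising after the injection visit that are recorded, equal in both arms.

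- A true risk p is recorded as c × p, and a true risk difference is also multiplied by c.
- With no recorded bleeds among 42, the one-sided 95% upper bound on recorded risk is 1 − 0.05^(1/42) = 6.9%. On true risk it is that bound divided by c.
- Power is for a two-sided Fisher exact test at 5%, 42 per arm, with the true risks multiplied by c.

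| Capture c (assumed) | Upper bound, no recorded bleeds | Power, 30% v 10% (assumed) | Power, 40% v 10% (assumed) |
|---|---|---|---|
| 100% | 6.9% | 56% | 87% |
| 75% | 9.2% | 40% | 71% |
| 50% | 13.8% | 20% | 44% |

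The first row reflects the size of the trial. Only the fall below it relates to this point.

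**The case against.** The strongest reply is that this is a condensed article. Its first safety sentence covers all adverse events, the questioning is introduced as something included rather than as the whole, and a case report form not shown may hold a fuller list. Much of this stands: unrelated events are not excluded, and the absence of a bleeding checklist would not by itself be a finding. What remains is that the article states a method, and the questioning it chooses to describe is conditional on the patient's own view of cause.

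Other points also carry weight. Serious adverse events go to the ethics commission with no relatedness condition, although someone must first report them. Haemarthrosis in the injected knee is easy to link to the injection. The condition is permissive, since the patient need only think a link possible. That patients would stay silent about a bleed is a plausible mechanism that the document neither supports nor refutes. The risks and capture rates in the table are assumptions, and a 30-point excess after one injection is extreme.

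Three stronger readings are tempting, and the document does not support them:

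- **Bias between arms.** A reader may note "A study nurse will have access to the randomization result and the allocated intervention" and infer that an unblinded nurse records events differently by arm. The article does not say that this nurse makes the follow-up observations, and the Data management section describes a study nurse who is blinded. Participants are blinded too, so any filter they apply is expected to act similarly in both arms.
- **Haematologic status goes unassessed.** It does not: the dyscrasia is an entry criterion, and eligibility is checked through "history taking, imaging examination, and laboratory tests".
- **Bleeds will be missed.** The text supports only that they may be.

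**Conclusion.** The point holds in a limited form. Bleeding between visits that a participant attributes to the underlying disorder is not actively sought by any method the article describes, and may be under-recorded in both arms. The expected consequence is lost sensitivity for harm, which makes a reassuring safety result less informative.

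The size of the loss cannot be estimated from the document; the illustrative figures show direction and mechanism only. The conclusion assumes that the Safety section describes the questioning used at follow-up and that some patients would put a bleed down to their disease. The primary WOMAC analysis and the sample size are unaffected. This is an inexpensive improvement worth considering, not an error that threatens the trial.

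**What to change.** In the Safety section, delete the condition that the participant must believe the event may be related. State instead that at 1, 3, 6 and 12 months the coordinating researcher asks every participant about any adverse event since the last visit, whatever its perceived cause, with prompts for bleeding, haemarthrosis and transfusion, and that these are reported by arm.

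The coordinating researcher is the natural choice. That role is blinded: "The patients, treating physicians and coordinating researchers will all be blinded to the allocation of the intervention". The Loss to follow-up section also already commits it to "contacting every patient and being present at every patient visit".

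The cost is a few fixed questions at four existing visits, with no new sampling. The drawback is that more background events from the underlying disease will be recorded and will have to be reported for both arms.

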### Loss to follow-up

The coordinating researchers will attempt to reduce loss to follow-up as much as possible by contacting every patient and being present at every patient visit. Each patient will be assisted by a coordinating researcher to ensure that each paper-based questionnaire is filled in. If the patient is lost to follow-up, an analysis of demographic and prognostic characteristics will be performed on these cases and the remaining patients. The patient eligible for and compliant with each follow-up will be documented.

### Missing items

If the proportion of missing data exceeds 10%, missing outcome data will be imputed using multiple imputation methodology and the sensitivity of the missing at random assumption will be investigated [24].

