### Sample size calculations

The sample size calculation is based on the primary outcome measure, the WOMAC score at 12-month. Based on previous studies, [5, 16, 17, 25] a 11.5 points reduction in WOMAC total score was considered as the minimum difference to be detected between the groups with a standard deviation (SD) of 16. Accepting a false-positive rate of 5% (α = 0.05) and a power of at least 90% (β = 0.10), we determined a theoretical minimum sample size of 84 patients. Considering the estimated 15% dropout rate, a total of 50 patients per group were required. Patient recruitment will be terminated in both groups when the required minimum number of patients is attained.

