### Statistical analysis

We will conduct an intention-to-treat analysis whereby all participants will be included in the study in the group to which they were randomized. The analysis will be conducted by a statistical expert blinded to the trial, with two-sided hypothesis tests and *p*-values < 0.05 significant.

Baseline characteristics will be analyzed between groups using descriptive statistics. Continuous variables will be expressed in terms of the means and the standard deviations, and compared using the student t test (normally distributed) or Mann-Whitney U test (nonnormally distributed). The categorical data will be expressed as frequency and compared using the Chi-square test or Fisher’s exact test. Normality will be confirmed using the Kolmogorov-Smirnov test.

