### Primary outcomes analysis

To test for the effect of treatment on the between-group difference in the primary outcome (WOMAC score), we will use a repeated measurement general linear model (GLM) with Sidak test for multiple comparisons. Changes from baseline to all follow-up time points (1-, 3-, 6- and 12-month) will be included in the model to assess the differences in the primary outcome at different follow-up times. The GLM will also be used as a multivariate analysis to assess the influence of the treatment on the follow-up evolution of all the clinical scores and objective measures performed. The mixed linear regression model (MLM) will be used to assess whether PRP effects on the primary outcome at 12 months will be moderated by age, body mass index, and Kellgren and Lawrence grade. The between-group differences of continuous, normally distributed and homoscedastic data will be compared for their means using the analysis of variance (ANOVA). Nonnormal data will be compared using the Mann-Whitney U test.

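### At or below 10% missing data the plan sets no imputation and no missing-at-random check, and the primary repeated-measures GLM, read classically, would then exclude anyone with a missed visit, against the intention-to-treat statement

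*Protocol article*

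**What the plan says.** Four parts of the protocol article bear on this point.

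- **Statistical analysis:** the analysis is by intention to treat, and "all participants will be included in the study in the group to which they were randomized".
- **Primary outcomes analysis:** for WOMAC, "we will use a repeated measurement general linear model (GLM) with Sidak test for multiple comparisons". On the data entering it: "Changes from baseline to all follow-up time points (1-, 3-, 6- and 12-month) will be included in the model". A mixed model is named separately and given a different job, a look at three baseline factors (age, body mass index and radiographic grade) as possible effect modifiers: "The mixed linear regression model (MLM) will be used to assess whether PRP effects on the primary outcome at 12 months will be moderated".
- **Missing items:** "If the proportion of missing data exceeds 10%, missing outcome data will be imputed using multiple imputation methodology". The same sentence goes on to say that "the sensitivity of the missing at random assumption will be investigated". There is no rule for 10% or less, and the text does not say whether the 10% is of values, visits, participants or 12-month scores.
- **Sample size calculations:** the calculation rests on WOMAC at 12 months and gives a minimum of 84 patients. "Considering the estimated 15% dropout rate, a total of 50 patients per group were required".

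**The concern.** A classical repeated-measures GLM treats the four change scores as one multivariate response and uses only participants who have all four. The protocol gives the name mixed model to a separate analysis, so the classical procedure is the natural reading of GLM here. At or below the threshold, nothing in the text then keeps a participant with one gap in the primary model. Someone who misses month 1 but attends month 12 would not count in the 12-month comparison on which the trial was sized.

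Two things are at stake. One is validity: if visits are skipped because of pain or lack of response, which is plausible when participants are asked to avoid analgesics for a year, the remaining complete cases are a selected group, and no sensitivity analysis is planned in that range. The other is precision: a modest share of missing values, spread over different people, can remove many participants without switching imputation on.

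**Working it through.** **Inputs from the protocol.** Difference 11.5 points, SD 16, two-sided α = 0.05, power 90%, 1:1 allocation, 84 evaluable, 15% dropout, 50 per group, four post-baseline visits. **Assumptions of this check.** The missingness patterns below, and, where stated, a denominator of 100 × 4 = 400 post-baseline values.

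**Step 1: the plan's own figure.** Power is that of the two-sample t test, with noncentrality 11.5 / (16 × √(2/n)) and 2n − 2 degrees of freedom, n being the number per arm. At n = 41 power is 89.5%; at n = 42 it is 90.2%. So 42 per arm, 84 in total, reproduces. (The normal approximation gives 41 per arm, 82 in total.) Then 42 / 0.85 = 49.4, rounded up to 50 per arm. The sample size is not in dispute. With all 50 per arm fully observed, power would be 94.5%, an upper bound.

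**Step 2: does the planned 15% dropout trigger imputation?** Take 15 of 100 participants lost.

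- Counted at 12 months: 15/100 = 15%. Triggered.
- Counted over 400 values, losses spread evenly over the four visits: (3.75 + 7.5 + 11.25 + 15) / 400 = 37.5/400 = 9.4%. Not triggered.
- Counted over 400 values, all losses after month 6: 15/400 = 3.75%. Not triggered.
- Counted over 400 values, all losses before month 1: 60/400 = 15%. Triggered.

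The same expected dropout therefore falls on either side of the switch, depending on a denominator that the text does not give. Where it is not triggered, a complete-case GLM uses 85 participants. Power is then 90.6%, so the stated power survives. What is lost is the earlier data of the 15 and the missing-at-random check.

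**Step 3: complete cases at the limit.** Suppose 10% of the 400 values, 40 in all, are missing.

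| Pattern of gaps | Complete cases | Power |
|---|---|---|
| Same people: 40/4 = 10 participants | 90 | 92.1% |
| Independent across visits: 100 × 0.90⁴ | about 66 | about 82% |
| Every gap in a different person: 100 − 40 | 60 | 78.2% |

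With 5% missing, independent gaps leave 100 × 0.95⁴ = 81.5 complete cases (89.3%), and gaps all in different people leave 80 (88.8%). Both counts are below the protocol's minimum of 84.

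**Step 4: a different denominator.** If the 10% counts participants with any gap, at most 10 of 100 can be excluded before imputation starts. The floor is then 90 complete cases and 92.1% power. The lower rows of the table depend on counting over values or visits.

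**The case against.** The strongest reply is that no section prescribes complete-case analysis. Deletion is how the classical procedure behaves, and a likelihood-based fit would keep partial data. A condensed article may also leave the handling of small amounts of missing data to a fuller document. Part of this stands: the conflict is conditional on the classical reading. But the article does fix both a primary model and a missing-data rule, and it reserves the mixed model for moderation, so the point concerns what was chosen and not only what was left out.

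A reader might infer three stronger things that the text does not support.

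- *That the plan drops everyone with a missed visit.* Above 10% multiple imputation is planned, and nobody need be dropped.
- *That the trial will be underpowered.* Gaps concentrated in the same people, as in ordinary dropout, leave power above 90%. The section on loss to follow-up also describes staff contacting every patient and helping with each questionnaire, which makes scattered gaps less likely.
- *That the threshold lets the results steer the analysis.* The rule is stated in advance, depends on the amount of missing data and not on treatment results, and the analyst is blinded. The handling of the primary outcome does still turn on observed missingness through an undefined proportion.

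The planned comparison of lost and remaining patients is useful description but does not replace a sensitivity analysis.

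**Conclusion.** The point holds in a limited range. At or below 10% missing data there is no stated imputation and no stated check of missing at random. On the natural reading of the primary model, participants with any missed visit would leave the analysis, contrary to the intention-to-treat statement. The undefined denominator makes this more than a marginal case, because the trial's own expected dropout may not reach the trigger.

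The effect on power is possible and not certain: about 78% to 92% at the 10% limit, against the stated 90%. This rests on counting over post-baseline values, on the assumed patterns of gaps, and on the protocol's own difference and SD in a two-sample comparison at 12 months. The exclusion of randomised participants does not depend on the pattern of gaps, only on the classical reading. Any bias would depend on why visits are missed and cannot be sized from the document.

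**What to change.** - Make the primary analysis a likelihood-based mixed model for repeated measures with treatment, visit, treatment-by-visit and baseline WOMAC. Use every observed visit of every randomised participant, and take the 12-month contrast as the primary result. Multiple imputation whatever the proportion missing, followed by the planned model, is an acceptable alternative.
- Delete the 10% trigger, which also removes the need for a denominator.
- Run the sensitivity analysis to the missing-at-random assumption unconditionally, for example by delta-adjusted imputation.

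The cost is a change of wording and slightly more analysis work in standard software. No new data or participants are needed. The change should be fixed before unblinding.
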